#### Health-related quality of life and patient-reported outcome measures

Cost-effectiveness will be analyzed by estimating incremental cost and effectiveness based on, patient life-years gained and quality-adjusted life years [QALY]) gained. These will also be modeled based on adherence to best evidence-based practices and anticipated outcomes. QALYs will be calculated based on health-related quality of life as measured by the EQ-5D-5L and the PedsQL in children.

PROMs analysis will be conducted by quality-of-life assessment using the ESAS-r and/or the IPOS-renal scales [22]. This data will be collected at first chronic dialysis session. Quantitative analysis will be done to assess changes in scores using a linear mixed effects model with the baseline score as a fixed effect co-variate, and dialysis unit, with each cluster as a random intercept.

All statistical analyses will be done using SAS Enterprise Guide 7.1 (Cary, NC), TreeAge Pro (TreeAge Software Inc., Williamstown MA) and Excel (Microsoft, Redmond VA).

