**Discussion:**

Dialyzing Wisely will implement, monitor, and report a suite of KPIs of acute KRT, coupled with a care pathway that will transform the quality of acute KRT across ICUs in Alberta. This program will provide a framework for scaling evidence-informed approaches to monitoring and management of acute KRT in other jurisdictions. We anticipate improvements in acute KRT performance, decreased healthcare system costs and improved patient quality of life by decreasing patient dependence on maintenance dialysis.

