#### Time of KRT initiation

The STARRT-AKI trial found that standard initiation of acute KRT was not associated with increased mortality. However, accelerated initiation was found to lead to a higher occurrence of adverse events and a 74% relative increase in risk of failure to recover kidney function and remain on maintenance KRT at 90-days when compared to the standard delayed initiation strategy [5]. While these findings were published in 2020, there has been no formal process through which to integrate them into clinical practice in Alberta ICUs.

The implementation of the Dialyzing Wisely evidence-based care pathway would provide a standardize means of integrating new and evolving evidence-informed best care practices. In addition, practitioners would have a standard mechanism through which to improve practice utilizing strategies such as audit and feedback, benchmarking and interactive peer group learning.

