### Population and eligibility

The inclusion criteria will be critically ill patients (i.e., adults and children) receiving acute KRT as part of their routine ICU care. No exclusion criteria will be applied.

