### Secondary outcomes

Length of KRTICU and hospital lengths of stayICU and 90-day mortalityRates of KRT dependence at 90 daysHealth-related quality of life measurement (i.e., EQ-5D-5L and PedsQL) and patient-related outcome measures (PROMs) (i.e., ESAS-r and IPOS-renal)

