APACHE II Score	number
SOFA score	number
Invasive/non-invasive ventilation	hrs/min
Vasopressors (include type)	hrs/min
CRRT/IHD/SLED	hrs/min
Cumulative daily fluid balance prior to RRT	mls
Creatinine, urea, pH, bicarbonate, potassium on day of RRT initiation	result
Renal Recovery at ICU Discharge	y/n - IHD
Renal Recovery at Hospital Discharge	y/n – IHD/PD
Renal Recovery at 6 Months	y/n - IHD/PD
ICU Mortality	A/D
Hospital Mortality	A/D
6-month Mortality	A/D
ICU length of Stay	days
Hospital Length of Stay	days
Number of admissions to site	aggregate
Patient days	aggregate
Ventilator days	aggregate
RRT days	Days CRRT/IHD/SLED
CRRT and IRRT data - filter life, reasons for retiring filters, treatment time lost, prescription/dose, machine alarms, machine down times, type of coagulation, blood flow rates, filtration fraction, adverse events, solute clearance, ultrafiltration realized	aggregate
Economic data - cost of filters, fluids, anticoagulation medications, RRT catheters, patient life-years gained, quality of life adjusted years (QUALY), re-hospitalizations, recurrence/chronic RRT, health care provider related costs	aggregate
QOL and PROMs	aggregate

Data sources will include multiple Alberta Health Services administrative databases, the Nephrology Information System (NIS) and the Patient Based Renal Information System (PARIS) (Supplementary Table 1) [20, 21].

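### ESAS-r and IPOS-renal are scheduled only at the first chronic dialysis session, which does not fit a model of change from baseline and restricts any comparison to patients who reached a primary outcome

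*Protocol article*

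**What the plan says.** All references are to the protocol article.

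- **Instruments and timing** (Health-related quality of life and patient-reported outcome measures): "PROMs analysis will be conducted by quality-of-life assessment using the ESAS-r and/or the IPOS-renal scales". The next sentence reads "This data will be collected at first chronic dialysis session".
- **Model** (same paragraph): the analysis will "assess changes in scores using a linear mixed effects model with the baseline score as a fixed effect co-variate", with a random intercept for dialysis unit or cluster.
- **Status**: Secondary outcomes lists these PROMs without a time point. Table 4 (Data management) has only the row "QOL and PROMs aggregate".
- **Population** (Population and eligibility): "critically ill patients (i.e., adults and children) receiving acute KRT as part of their routine ICU care", with no exclusions.
- **Dialysis entry as an outcome**: the count of patients entering maintenance KRT programs is under Primary outcomes. The Discussion in the abstract anticipates "improved patient quality of life by decreasing patient dependence on maintenance dialysis".
- **Comparisons**: Health outcome measures, under Statistical analyses, plans general tests of baseline against intervention period. Subgroup analysis extends the subgroup work to the secondary outcomes and attaches a treatment-by-subgroup interaction test to each analysis.

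**The concern.** There are two separate problems.

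The first is internal. A change adjusted for baseline needs two scores per patient, and the article names one occasion. Since both timing and model are stated, and in adjacent sentences, this is a mismatch in the text and not merely a detail left to another document.

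The second would remain if later scores were collected. The study population is everyone receiving acute KRT in the ICU, but a PROM is scheduled only for those who go on to chronic dialysis. The pathway acts earlier, in the ICU, and is meant to change who gets that far. Dialysis starters before and after implementation would then be differently selected groups. A difference in their mean scores could reflect who was selected, a change in how patients feel, or both. The patients in whom the anticipated benefit would occur, those spared dialysis, have no scheduled PROM. A pathway that works could leave the measured mean unchanged, or make it look worse.

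**Working it through.** The article gives no sample size, power or effect size for PROMs, so there is no stated figure to reproduce. The check is mainly textual, with two illustrations of scale.

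**1. Timing against model.** Let Y0 be the baseline score and Y1 the follow-up score. The stated model needs Y1 − Y0 as outcome and Y0 as covariate.

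- If the first session is the outcome (Y1), no earlier score is planned and Y0 is undefined.
- If the first session is baseline (Y0), no later score is stated and Y1 is undefined. That baseline would also come after the ICU-stage pathway, so adjusting for it could remove part of any pathway effect.
- If one score serves as both, the change is zero for every patient.
- If baseline means a pre-implementation or unit-level mean, a model could be fitted, but the text does not say so and the selection problem stays.

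**2. Who is measured.** Population: all acute KRT patients. PROM sample: those who survive and start chronic dialysis. Dialysis entry: a primary outcome, occurring after exposure to the pathway. A period or treatment contrast within the PROM sample is therefore conditioned on a post-intervention event.

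**3. How far the measured group could shrink.** Input: the "74% relative increase in risk of failure to recover kidney function and remain on maintenance KRT at 90-days" cited under Time of KRT initiation for accelerated against standard initiation, that is, a ratio of 1.74. Assume the whole excess is present at baseline and a fraction h of it is removed. The proportional fall is 1 − (1.74 − 0.74h)/1.74 = 0.74h/1.74.

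| h | Fall in assessed group |
|---|---|
| 0.25 | 10.6% |
| 0.50 | 21.3% |
| 1.00 | 42.5% |

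For a rough head count, Acute KRT in Alberta gives 56 additional ESKD patients a year and 1278 acute KRT patients in 2019. The article does not show how the 56 was derived. Assuming it comes from the same ratio:

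- All patients exposed to the excess: 56/0.74 ≈ 76 a year without it and 76 + 56 = 132 with it. These are 76/1278 = 5.9% and 132/1278 = 10.3%, so 89.7% to 94.1% would have no PROM.
- Only half exposed: 56/(0.5 × 0.74) ≈ 151, and 151 + 56 = 207 with the excess, or 207/1278 = 16.2%.

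The 1278 includes patients who die and could never give a score.

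**4. What selection alone could do.** Assume a standard normal severity S, a score with unit SD in the whole acute KRT population (higher is worse) and correlation r with S, and dialysis when S exceeds a cut-off. The pathway changes no one's score and only divides dialysis risk by 1.74. The shift in the measured mean is r × [φ(c1)/p1 − φ(c0)/p0], where p1 = p0/1.74 and c0, c1 are the matching normal cut-offs. Simulated values, in SD:

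| Baseline risk p0 | r = 0.3 | r = 0.5 | r = 0.7 |
|---|---|---|---|
| 6% | 0.071 | 0.112 | 0.159 |
| 10% | 0.077 | 0.125 | 0.174 |
| 15% | 0.081 | 0.134 | 0.190 |

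Every shift is towards worse because the assumption is that the sicker patients still reach dialysis. If averted cases were unrelated to the score the shift would be zero, and if they were mainly those with the worst scores its sign would reverse. The values of p0 and r are assumed; the article gives neither.

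**The case against.** The article nowhere says that the scores are collected once, or only then. The first session could be the baseline for later assessments set out in a full protocol or SAP that is not shown. **This stands in part**: a reader might infer that the model cannot be fitted at all, and the text does not establish that. What it establishes is a stated timing and a stated model that do not match.

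The PROM model as described has no pathway or period term, so it might only describe trajectories among incident dialysis patients, in which case selection biases no pathway effect. This would answer the second problem if the PROM paragraph stood alone. It does not: Subgroup analysis calls for treatment interaction tests on the secondary outcomes, and the general before/after tests can also be read to cover them.

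The anticipated quality-of-life gain is not said to rest on ESAS-r or IPOS-renal. Maintenance KRT entry, 90-day KRT dependence, mortality and renal recovery are captured, and averted ESKD and QALYs are modelled. **This stands**: a reader might infer that the benefit is never assessed, but the supportable point is only that these two PROMs, as scheduled, cannot show it.

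The Table 4 label might be taken to rule out a patient-level model. It does not: the same label covers filter life, adverse events and costs, and may simply mark grouped rows.

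**Conclusion.** The point holds in two parts. The stated PROM timing and the stated change model do not fit and must be reconciled. Any pathway comparison of these scores is also made within a group defined by a primary outcome, so it cannot show benefit in patients who avoid dialysis.

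The selection follows from the design as written; its size does not. The 42.5% shrinkage is the case in which the full 74% excess is present and then removed. The 0.07 to 0.19 SD shift depends on the assumed risk, correlation and selection mechanism, and its direction on which patients are averted. The supportable statement on coverage is that most of the cohort has no scheduled ESAS-r or IPOS-renal score. A firm minimum of 90% is not supported, since one end of the calculation leaves 89.7% and its derivation is assumed.

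A reader might extend the point to EQ-5D-5L, PedsQL and the QALY analysis. The documents do not support that: the timing sentence follows the ESAS-r/IPOS-renal sentence, and no timing is given for the other instruments. The consequence is confined to one secondary outcome; the primary outcomes are unaffected.

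**What to change.** 1. **Reconcile timing and model.** If the first-session score is the only one, delete the reference to change and the baseline covariate, and summarise the score cross-sectionally with a dialysis-unit random intercept. If later scores are collected, state the time points and define the first-session score as baseline.
2. **Limit the claim.** In either case, label the ESAS-r/IPOS-renal analysis as descriptive for incident dialysis patients.
3. **Remove it from effect testing.** Exclude these scores from the before/after tests and the treatment-by-subgroup interaction tests. Adding a pathway indicator with case-mix adjustment is no substitute, because it is still a comparison within the selected group.
4. **Do not cite it for the anticipated benefit.** State that these scores will not be used to support the quality-of-life gain anticipated in the abstract.

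If only the first-session score exists, this costs wording and no extra assessments. The price is a weaker claim for one secondary outcome.

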### Subgroup analysis

Pre-specified subgroup analysis will include ICU patients to 1) adult vs. children, 2) female vs. male, 3) academic vs. community/regional ICUs, 4) cardiovascular ICUs vs. Cardiac ICU vs. medical/surgical ICUs, 5) high KRT volume vs. low KRT volume centers (i.e., as per quartiles).

We will perform the above analyses for health economic evaluations, patient and process of case measures to include our pre-specified primary and secondary outcomes for each subgroup. Each analysis will be accompanied by a test for interaction between treatment and subgroup to ascertain whether effects differ significantly between subgroups.

### Ethics approval and consent to participate

This evaluation was reviewed by the University of Alberta Health Research Ethics Board (HREB) and a waiver of consent was granted based on the premise this project represents health services implementation and evaluation compatible with a quality assurance and improvement initiative.

### Knowledge translation and dissemination

Dialyzing Wisely is largely a program focused on knowledge translation and implementation of an acute KRT pathway based on evidence-based best practices.

Throughout the project period Clinical Practice Leads will review sub optimally performing KPIs across acute KRT programs and provide targeted education to individual ICU teams to best understand opportunities to drive improved performance. The Clinical Practice Leads will also facilitate the implementation of evidence-based best practices into clinical practice through individualized prescriber reports regarding acute KRT initiations and bedside provider education.

We will publish two peer-reviewed manuscripts for the Dialyzing Wisely program, one outlining the protocol, and the second disseminating study results. Additional manuscripts may be developed to present subgroup findings as well as patient-centered outcomes including PROMs. In addition, the results of the Dialyzing Wisely program will be presented at local, provincial, and national critical care and nephrology meetings.

## Discussion

In Alberta, we do not routinely measure when we initiate acute KRT, or how well we perform this therapy in ICU settings. We recognize there are KPIs that can be implemented that are not used routinely in clinical practice [9, 23, 24]. These are missed opportunities to improve the quality and safety of care, reduce unnecessary practice variation and address an important evidence-to-care gap on one of the key life-support technologies used in ICU [23–26].

Using the Quality Enhancement Research Initiative (QUERI) Roadmap for Implementation and Quality Improvement, the Dialyzing Wisely program will use a pragmatic strategy on how to adopt, adapt, implement, spread and sustain these evidence based clinical practices and innovations across an entire healthcare system [27]. This pathway will use the Learning Health System Knowledge to Action Framework with the principles of robust pre-implementation planning, followed by appropriate implementation strategies to ensure the sustainability of the program after the transition of ownership of the program to local stakeholders [16]. Having the implementation of the acute KRT pathway follow the roll-out of our CIS will ensure that the program will continuously seek to generate and learn from local data in order to improve systems and individual performance and enhance individual health and quality of care [28, 29]. To date, care gaps have been identified and a solution determined based on recently published evidence. Local stakeholders have been engaged and consulted in the development of the pathway. Evidence-based change techniques will be utilized to enact change across units, adapting to local policies and workflows to ensure the seamless integration of the acute KRT pathway into each ICU [30]. Our study team has previously embarked on a similar program of work, QUALITY CRRT, which aims to improve solely the performance of CKRT in our ICUs [31]. Dialyzing Wisely will expand on this work to not only evaluate KPI’s for CKRT, but for the provision of IKRT and prescriber practices as well in order to transform the delivery of acute dialysis throughout the critical care healthcare system.

The Dialyzing Wisely program will build on the infrastructure within our CIS to develop a easy and simple way for monitoring KPIs, to report progress to stakeholders and make data accessible to each ICU. Finally, to transition ownership to each ICU and associated stakeholders, we will work with our partner organizations to ensure the appropriate management support for each program to support continuous learning from knowledge gained throughout the Dialyzing Wisely initiative.

## Limitations

Dialyzing Wisely looks to improve the performance of acute KRT. However, this program does not address the care of patients with pre-existing chronic kidney disease (CKD) with dialysis initiated as part of a long term management plan. These patients are the majority of patients with new ESKD who enter long term chronic dialysis programs. We will share the experience gained in Dialyzing Wisely with other teams managing ESRD in order to facilitate and promote the monitoring of KPIs in this patient population.

Finally, the discontinuation or modality choice of acute dialysis is not part of the Dialyzing Wisely acute dialysis pathway. This is in large part due to the lack of evidence-based protocols for weaning and discontinuation from acute KRT, or transition from CKRT to IKRT. However, Dialyzing Wisely will build a framework that can be utilized for the implementation of new evidence across our ICUs and acute dialysis prescribers once it becomes available.

## Conclusion

Dialyzing Wisely will implement an acute dialysis care pathway across Alberta ICUs in order to improve the performance of acute dialysis, ensure prescribers follow best-evidence based practices, and decrease healthcare system costs while improve the quality of lives of people living in Alberta.

## Data Availability

Not applicable.
